## Abstract

**Background:**

Dyspnea is a common cause of hospitalization, posing diagnostic challenges among older adult patients with multimorbid conditions. Chest computed tomography (CT) scans are increasingly used in patients with dyspnea and offer superior diagnostic accuracy over chest radiographs but face limited use due to a shortage of radiologists.

**Objective:**

This study aims to develop and validate artificial intelligence (AI) algorithms to enable automatic analysis of acute CT scans and provide immediate feedback on the likelihood of pneumonia, pulmonary embolism, and cardiac decompensation. This protocol will focus on cardiac decompensation.

**Methods:**

We designed a retrospective method development and validation study. This study has been approved by the Danish National Committee on Health Research Ethics (1575037). We extracted 4672 acute chest CT scans with corresponding radiological reports from the Copenhagen University Hospital–Bispebjerg and Frederiksberg, Denmark, from 2016 to 2021. The scans will be randomly split into training (2/3) and internal validation (1/3) sets. Development of the AI algorithm involves parameter tuning and feature selection using cross validation. Internal validation uses radiological reports as the ground truth, with algorithm-specific thresholds based on true positive and negative rates of 90% or greater for heart and lung diseases. The AI models will be validated in low-dose chest CT scans from consecutive patients admitted with acute dyspnea and in coronary CT angiography scans from patients with acute coronary syndrome.

**Results:**

As of August 2025, CT data extraction has been completed. Algorithm development, including image segmentation and natural language processing, is ongoing. However, for pulmonary congestion, the algorithm development has been completed. Internal and external validation are planned, with overall validation expected to conclude in 2025 and the final results to be available in 2026.

**Conclusions:**

The results are expected to enhance clinical decision-making by providing immediate, AI-driven insights from CT scans, which will be beneficial for both clinicians and patients.

**International Registered Report Identifier (IRRID):**

DERR1-10.2196/77030

## Introduction

### Background

Dyspnea accounts for up to 15% of all acute hospital admissions [1], and patients with dyspnea are often older adults and have multimorbid conditions. Correctly diagnosing the cause of dyspnea as either heart or pulmonary disease in emergency settings can be challenging, and 20% of the patients with acute heart failure are initially misdiagnosed [2]. Chest radiographs have long been the primary diagnostic tool for acute dyspnea [2]. However, cardiac decompensation and signs of pneumonia are often overlooked on chest radiographs, especially in older adult patients with chronic lung disease [3]. In addition, many patients with acute dyspnea cannot stand while undergoing chest radiographs, which further limits their diagnostic value.

Chest computed tomography (CT) scans offer the highest standard of care modality for patients with comorbid conditions and emergent conditions, such as pulmonary embolism, aortic dissection, pneumothorax, and chest trauma. Moreover, the diagnostic use of CT imaging for patients with dyspnea has increased [4]. CT scans allow for fast image acquisition and depict anatomy in cross section and 3 dimensions, providing superior information compared to conventional chest radiographs on diseases in the pulmonary parenchyma, heart, and vessels [5]. In our previous work, we identified 5 characteristic CT signs that were strongly associated with acute heart failure in patients with dyspnea [6] and later demonstrated that CT was 4 times more likely than chest radiography to detect cardiac decompensation in the emergency department [7]. Building on these findings, we now aim to enable automatic detection of cardiac decompensation on CT.

With an expected increase in older adults and patients with comorbid conditions admitted with dyspnea, there will be a greater need for accurate and fast diagnostic methods in the emergency departments. Over the course of the last 2 decades, there has been a worldwide increase in the number of CT scans [4]. In combination with a shortage of radiologists, this limits the broad use of chest CT imaging for patients with acute dyspnea in the emergency setting [8]. Automated diagnostic tools have the potential to enhance radiological efficiency by expediting the assessment and triage of patients presenting with acute dyspnea, thereby streamlining workflow in acute care settings. Conditions, such as cardiac decompensation, pneumonia, and pulmonary embolism, require timely diagnosis and intervention to improve clinical outcomes [1,2,9], making them appropriate targets for such models.

While the potential of artificial intelligence (AI) to support physicians in acute care is substantial, several challenges are particularly relevant for patients with dyspnea. Older adults and populations with comorbid conditions may introduce demographic bias and limit generalizability across settings, and variations in CT protocols, scanner types, and image quality can affect feature representation. Furthermore, interpretability is essential to ensure clinical applicability. In this protocol, we outline strategies to address these challenges by including diverse training data and multiple CT protocols and planning model outputs that are clinically interpretable with validation as a central component.

Previous AI studies have mainly focused on detecting pneumonia and pulmonary embolism on chest CT scans [10-15]. To our knowledge, no previous work has addressed the automated identification of acute heart failure on chest CT. This study introduces an algorithm capable of detecting all 3 conditions in the acute setting.

### Objectives

We hypothesize that AI algorithms can identify radiological conditions requiring urgent intervention with diagnostic accuracy comparable to current clinical radiology practice.

The aim of this protocol is to outline the framework for developing and validating AI algorithms to support this initiative. The proposed algorithms should be able to automatically analyze chest CT scans with the potential for providing immediate feedback on the likelihood of dyspnea-related diagnoses. The primary focus will be on cardiac decompensation, with the model also serving as a foundation for detecting pneumonia and pulmonary embolism.

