### Ground Truth for Development and Validation of the AI Algorithm

The ground truth for the development and validation will be the radiological description of each CT scan, prepared by the on-call radiologist following standard clinical procedures. The on-call radiologists include both board-certified specialists and junior radiologists in training. All final assessments are supervised by a board-certified radiologist. All radiological reports are produced as part of routine clinical practice, and while variations in descriptions may occur due to specific clinical focuses of the scans, the regional standard reporting procedures ensure a consistent approach to assessing pathologies. These radiological findings will be extracted from the radiology reports (PDF) using a set of regular expressions for the selected diseases. The report clinical labels for cardiac decompensation may encompass terms such as pulmonary congestion, pulmonary edema, heart failure, and decompensation in the description of the radiologist. A subset of training data will be used to iteratively improve expressions. All reports containing these indicators, whether affirming or negating their presence, will be manually reviewed to correct any labeling errors. All labels will be reviewed for technical accuracy, with unclear cases assessed by project clinicians. False positives and negatives will be evaluated by chief physicians specializing in thoracic radiology.

Given the large volume of scans, manual review by an expert radiologist is impractical and resource intensive, but this approach maximizes the dataset, reflects real-world workflow, and mitigates risks to model validity.

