**Exclusion criteria for the CATCH study (none of the exclusion criteria must be met)**
Aged <18 yearsNew diagnostic ECG changes with ST-segment elevation or depression >0.5 mm or T-wave inversion >4 mm in ≥2 contiguous leadsWomen of childbearing age not using approved contraceptionGeographical residence or mental or physical conditions that could complicate follow-upKnown allergy to iodinated contrast agentsSerum creatinine >130 mg/LAbnormal chest radiography or blood test results that could explain chest painPrevious coronary artery bypass graftingPatients who refused or could not provide consent

The primary outcome is to validate the diagnosis of the AI algorithm in identifying the following: (1) normal CT images without treatment-requiring pulmonary changes, (2) radiological signs of cardiac decompensation, and (3) radiological infiltrates indicative of pneumonia.

The gold standard is the radiological evaluation of the CT images, which were analyzed in 2 ways:

Randomly analyzed by the on-call clinical radiologists according to clinical standards. The on-call radiologists had access to the medical journal, laboratory reports, and previous radiology images. The workflow is as follows: a radiology report is made by the on-call clinical radiologist and subsequently approved by a senior radiologist.Two blinded, independent specialist thoracic radiologists evaluated every CT scan for distinct signs of heart and pulmonary diseases according to the Fleischner Society list [7,22].

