Fourth, although the AI model will be trained on well-characterized cohorts, its future performance may be affected by variations in demographic, technical, and clinical factors outside the study setting. Demographic differences, such as age, sex, and comorbidities, could influence the appearance of the disease on CT scans. Technical factors, including scanner models, acquisition parameters, and image reconstruction methods, may alter feature representation and introduce site-specific biases. Clinical workflow differences, such as referral patterns or labeling practices, could further affect the distribution and definition of target conditions. These challenges are inherent to all nonmulticenter studies. Consequently, the algorithm will likely require further adaptation and validation before being deployed commercially or applied globally. To mitigate these issues, this protocol emphasizes standardized labeling procedures and the inclusion of diverse training data with multiple scanning protocols and scanner brands. In addition, external validation across diverse populations and imaging settings is needed to further strengthen the model.

Successful clinical implementation will also require regulatory approval, user-friendly integration, and appropriate clinician engagement. If the developed AI model demonstrates satisfactory performance in the planned validation cohorts, subsequent work will examine how best to integrate it into routine clinical workflows; however, this is not encompassed by this protocol. Finally, potential risks of AI, including clinician overreliance and false negative results, must be carefully considered. AI outputs are intended to support, not replace, clinical judgment.

A strength of this study is that the AI algorithms will be developed in a cohort of undifferentiated patients from all medical departments ordering acute scans. We included diverse CT images conducted with different scan protocols, reconstruction kernels, and scanner models and vendors, both contrast and no contrast and low dose and high dose. The FACTUAL patient cohort for the validation is well validated, with comprehensive and detailed radiologic labels provided by 2 blinded thoracic expert radiologists.

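### No planned analysis tests the hypothesis of accuracy comparable to current radiology practice: the on-call report serves as reference and never as comparator, although FACTUAL holds the reads needed for a comparison

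*Protocol article*

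**What the plan says.** All references are to the protocol article.

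- **Objectives** gives the hypothesis: "We hypothesize that AI algorithms can identify radiological conditions requiring urgent intervention with diagnostic accuracy comparable to current clinical radiology practice". It does not define comparable.
- **Ground Truth for Development and Validation of the AI Algorithm** sets the reference: "The ground truth for the development and validation will be the radiological description of each CT scan, prepared by the on-call radiologist". The same section says that "All radiological reports are produced as part of routine clinical practice", so this reference is current practice.
- **Validation in Chest CT Scans in the Clinical FACTUAL Cohort** (the text after the eligibility box) says: "The gold standard is the radiological evaluation of the CT images, which were analyzed in 2 ways". The first way is "Randomly analyzed by the on-call clinical radiologists according to clinical standards", by readers who could see the patient record, laboratory results and previous images, with approval by a senior radiologist. The second is "Two blinded, independent specialist thoracic radiologists evaluated every CT scan for distinct signs of heart and pulmonary diseases". Neither is named as the governing read.
- **Statistical Analyses** carries the thresholds from internal validation into each cohort and lists odds ratios, sensitivity, specificity, predictive values, likelihood ratios and the area under the curve, all for the AI. No such measure is listed for the on-call read.
- **Strengths and Limitations** describes the on-call description as ground truth for development and internal validation, and admits that reports can be wrong. It counts as a strength of FACTUAL its "comprehensive and detailed radiologic labels provided by 2 blinded thoracic expert radiologists". It also says that VERDICT and CATCH have no radiological reports.

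**The concern.** To show that a new reader performs about as well as an existing one, both must be scored against a third source of truth. Here the existing reader supplies the truth. Scored against itself, on-call practice has 100% sensitivity and specificity by construction. Every disagreement then counts as an AI error, including those where the AI is right and the report missed the finding.

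FACTUAL is the one cohort with a possible third source. Its two reads sit under a single label, so each primary outcome item could yield two sets of sensitivity and specificity, and either could be quoted. Even with the expert read as reference, the listed measures would give the AI's accuracy but not that of current practice on the same scans. The study could finish with its stated hypothesis unanswered, or with agreement figures presented as an answer.

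**Working it through.** **The plan's own figure.** None is attached to this hypothesis. The Power Calculation section gives about 5000 scans, against an initial estimate of at least 15,000, with no margin, precision or expected accuracy. There is nothing to reproduce, so the check sets the passages side by side and then uses illustrations for scale.

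**Step 1. What each cohort can show as planned.**

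| Cohort | Reference | On-call read scored against another reference? | What results mean |
|---|---|---|---|
| Internal test set | On-call report | No; no second read of all scans | Agreement with routine reports |
| FACTUAL | On-call report and two-expert read, neither ranked | Possible, not planned | AI accuracy against either read; no contrast |
| VERDICT, CATCH | No radiological reports | No | Prognostic value |

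The internal test third holds about 4672/3 = 1557 patients. At 7% to 8% report-positive, that is 109 to 125 positives for decompensation. A larger set would not help, because there is no second reference.

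**Step 2. An always-correct AI scored against an imperfect report.** Let p be prevalence, Se and Sp the on-call accuracy.

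- Apparent sensitivity = p·Se / [p·Se + (1−p)(1−Sp)]
- Apparent specificity = (1−p)·Sp / [(1−p)·Sp + p(1−Se)]

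With Se = 0.80 and Sp = 0.95 (assumptions):

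| p | Apparent sensitivity | Apparent specificity |
|---|---|---|
| 7.5% | 0.060/(0.060+0.04625) = 0.565 | 0.983 |
| 20% | 0.16/(0.16+0.04) = 0.800 | 0.950 |
| 40% | 0.32/(0.32+0.03) = 0.914 | 0.877 |

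In the first two rows a reader better than current practice misses the 90% sensitivity target; in the third it misses the 90% specificity target.

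**Step 3. FACTUAL, effect of the choice of reference.** N = 242 is from the document. Assumed: p = 0.30, on-call sensitivity s = 0.80, no on-call false positives, and an AI that agrees with the experts on every scan.

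- Expert-positive: 242 × 0.30 = 72.6, about 73
- Missed by the on-call read, so scored as AI false positives: 72.6 × 0.20 = 14.5, about 15
- On-call negatives: 242 − 72.6 × 0.80 = 183.9
- Apparent specificity: 1 − 14.5/183.9 = 0.92, instead of 1.00

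Range: 0.976 at p = 0.2, s = 0.9; 0.833 at p = 0.4, s = 0.7.

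**Step 4. Precision of the comparison FACTUAL would allow.** The 95% half-width for a paired difference in sensitivity is 1.96 × √(d/n), where d is the proportion of expert-positive patients on whom AI and on-call disagree, with a true difference of zero. For n = 73:

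- d = 10%: 0.073
- d = 20%: 0.103
- d = 30%: 0.126

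If prevalence is 20% or 40% (48 or 97 positives), the half-width at d = 20% is 0.13 or 0.09. Power to exclude a 10-point loss in sensitivity at d = 20% (one-sided 2.5%, true difference zero) is 34%, 48% and 60% at prevalence 20%, 30% and 40%. For specificity the corresponding powers are 88%, 83% and 77%.

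**The case against.** **The documents already lean to the expert read in FACTUAL.** Strengths and Limitations ties on-call ground truth to development and internal validation, and presents the expert labels as what makes FACTUAL a good cohort. This stands. AI accuracy against the experts can come from the plan as it is. But the FACTUAL section still puts both reads under one gold standard, and the on-call read is nowhere scored against the experts.

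**Disagreements go to thoracic chief physicians.** False positives and negatives are to be reviewed, and the Results section lists this review as a milestone. That eases the harm of a correct AI being marked wrong. It is no substitute for a reference: there is no rescoring rule, and errors shared by AI and report are never examined.

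**The hypothesis is loosely worded, and the 90% target is the working criterion.** One can read success in the internal set as close reproduction of routine reports, which is testable. This is fair, and it points to the rewording below. A fixed target is still not a comparison with radiologists.

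**Some detail belongs in an analysis plan.** A margin and a rule for expert disagreement are commonly left there, and their absence from an article is not held against it. The point rests on what the article does state.

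**The comparison has limits.** The wording on random analysis leaves open whether every FACTUAL scan has an on-call read. On-call readers had clinical information, while the experts were blinded. Embolism is not validated in FACTUAL. All of this stands and limits what can be claimed.

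A reader might infer that the hypothesis cannot be tested at all. The documents do not support that: it is strictly so only for the internal set. In FACTUAL the reads needed are described as done, and the test is simply not planned.

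**Conclusion.** As planned, no analysis in any cohort tests whether the AI is comparable to current radiology practice. Internal validation measures agreement with routine reports. FACTUAL has an independent expert read but does not rank it above the on-call report, and the listed measures describe the AI only. VERDICT and CATCH cannot contribute.

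The structural point needs no numbers. The illustrations of its size rest on assumptions: FACTUAL prevalence, on-call sensitivity and specificity and the rate of discordance are not in the document. The 92% figure (range 83% to 98%) also assumes no on-call false positives, and the half-width of 7 to 13 points assumes about 73 positives and no true difference. On these figures a paired comparison is feasible but imprecise for sensitivity, and a 10-point margin test would often be inconclusive.

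**What to change.** 1. **FACTUAL section and Statistical Analyses:** name the blinded two-expert read as the FACTUAL reference standard, as Strengths and Limitations already implies, and make the on-call report a comparator.
2. **On patients with both reads:** report sensitivity and specificity of the AI at the threshold fixed beforehand and of the on-call report, with paired differences and 95% CIs. State how many of the 242 have both reads. Keep AI versus on-call agreement as a secondary analysis.
3. **State the limits:** the comparison covers cardiac decompensation and pneumonia only; on-call readers had records, laboratory results and earlier images; precision for sensitivity is limited. Comparability may be claimed only within the interval obtained.
4. **Objectives:** for the internal set, and for pulmonary embolism, restate the hypothesis as agreement with routine radiology reports.

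The cost is wording and one paired analysis of reads already described as done. No new data are needed, provided enough scans carry an on-call read. The drawback is that the interval may be too wide to support a claim of comparability, and the report must then say so. The reference should be fixed before FACTUAL results are seen, since a choice made afterwards would not be credible.

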## Methods

### Study Design

This is a retrospective study, including method development and validation (Figure 1).

**Figure 1 figure1:**
[figure not shown]
Overview of development and validation cohorts. We did not extract CT studies from participants from the FACTUAL study (year 2017-2019) or for patients below 18 years of age. CT: Computed Tomography; NSTE-ACS: non–ST-segment elevation acute coronary syndrome. Created with Biorender.

### Training and Internal Validation Cohort

We extracted CT scans with accompanying radiological reports from all medical departments at the Copenhagen University Hospital–Bispebjerg and Frederiksberg Hospital, Denmark, conducted from January 1, 2016, to December 31, 2021. Consequently, 12,348 CT scans from 5111 studies of 4672 individual patients were extracted (Figure 1).

The scans originated from all medical wards ordering acute CT scans as standard diagnostic procedures. All types of CT scans (chest CT and abdominal scans, including the lungs) were included, encompassing various manufacturers, contrast-enhanced scans, noncontrast scans, low-dose protocols, and various imaging phases. Given the comprehensive inclusion of all acute chest CT examinations, the indications for these scans were broad and included assessments of chest pain, dyspnea, suspected pulmonary embolism, suspected pulmonary infection, suspected pneumothorax, or pleural effusion. We did not extract CT scans for patients aged 18 years or younger and participants in the Feasibility of Computer Tomography in Patients with Acute Decompensated Heart Failure (FACTUAL) study, as it served as a clinical validation cohort [7].

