### Development of the AI Algorithm

We will develop an individual AI algorithm for automatic interpretation of radiologic signs of cardiac decompensation on chest CT scans, but the algorithm will also serve as a foundation for pneumonia and pulmonary embolism. The model will be trained to detect each condition, pulmonary congestion, pneumonia, and pulmonary embolism, independently, using a multilabel approach with separate binary classifiers. This allows more than one condition to be identified in the same scan. The CT scans were extracted in pseudonymized form.

Participants will be randomly split on the participant level into training (2/3) and internal test data (1/3; Figure 1). This process will be carried out separately for each of the 3 diseases, creating distinct AI models for each. We will train boosted tree prediction models using volume, diameter, and density measurements from structures segmented in the CT images. The segmentations will be derived from TotalSegmentator, extreme gradient boosting, and in-house codes [16,17].

We do not expect substantial missing data, as all CT scans will be extracted retrospectively without patient consent. Extreme, noisy, or missing feature values, typically caused by segmentation errors, will be handled by allowing them as many splits as possible in the tree-based model. To develop the model, a three-step procedure will be applied for boosted trees models: (1) parameter tuning with all features, (2) feature selection by forward selection guided by internal feature importance measures of extreme gradient boosting, and (3) retuning with the selected features. Hyperparameter optimization will be conducted by grid search using the area under the receiver operating characteristic curve as the evaluation metric. Parameter tuning and feature selection will be performed on the training data with stratified 3-fold cross validation, defined at the participant level and kept consistent across all steps.

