**Exclusion criteria for the FACTUAL study (none of the exclusion criteria must be met)**
All study examinations, including low-dose chest computed tomography (CT) scans, performed later than 12 hours after admissionPatients who are unstableRequiring ventilation (including noninvasive ventilation)Requiring intensive care (inotropic treatment)Requiring telemetry due to acute coronary syndromePatients who refuse or cannot provide consent (ie, mental illness [eg, dementia] and language barriers)Patients without Danish citizenshipLife expectancy <3 months (assessed by the emergency department physician)CT thorax already indicated (pulmonary embolism, aortic dissection, or aneurysm)Patients who are isolated (ie, vancomycin-resistant *Escherichia coli* and influenza)

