### Statistical Analyses

In each validation cohort, the default thresholds obtained from the internal validation will be used to calculate the diagnostic ability of the AI algorithm to predict the prespecified heart and lung diseases. We will, for all diagnoses, calculate odds ratios, sensitivity, specificity, positive and negative predictive values, positive and negative likelihood ratios, and area under the curve from the ROC curves.

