#### Mitigating Imaging Variability and Validation Thresholds

Differences in imaging protocols across cohorts, including variations in scanner type, reconstruction kernels, and acquisition parameters, may affect AI model performance. To address this, the algorithm will be developed using data from multiple manufacturers, image types, and reconstruction kernels, and it will include both contrast-enhanced and noncontrast scans. This approach is designed to minimize the impact of technical variability and improve generalizability across different clinical settings, reducing the risk of bias from scanner settings and acquisition protocols. Planned cross-cohort validation will further ensure the robustness of the algorithm.

The sensitivity and specificity thresholds of 90% or greater chosen for validation are ambitious, but they align with performance levels generally regarded as necessary for clinical decision support in acute care, where the consequences of false negatives and false positives can be substantial. Thus, these thresholds serve as a target for ensuring patient safety and diagnostic reliability. We acknowledge that achieving such levels may involve trade-offs, including impaired sensitivity-specificity balance or reduced generalizability due to increased model complexity. High false positive rates could burden clinicians with unnecessary alerts, while false negatives might delay diagnosis of critical conditions.

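### The pulmonary embolism classifier is developed and internally tested on a pool mixing contrast and noncontrast scans, with no stated rule for scans on which embolism cannot be assessed, so its pooled AUC and specificity may be inflated

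*Protocol article*

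**What the plan says.** Under Training and Internal Validation Cohort, the article describes a deliberately broad extraction: "All types of CT scans (chest CT and abdominal scans, including the lungs) were included, encompassing various manufacturers, contrast-enhanced scans, noncontrast scans, low-dose protocols". The yield is given as "12,348 CT scans from 5111 studies of 4672 individual patients were extracted". Mitigating Imaging Variability and Validation Thresholds repeats the mix for algorithm development, stating that "it will include both contrast-enhanced and noncontrast scans", and presents it as protection against bias. Strengths and Limitations counts it as a strength.

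Under Development of the AI Algorithm, "The model will be trained to detect each condition, pulmonary congestion, pneumonia, and pulmonary embolism, independently". The step described as separate for each disease is the random two-thirds to one-third split. The predictors are volumes, diameters and densities of segmented structures, and tuning maximises the area under the ROC curve.

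Under Ground Truth, the label is the routine report: "These radiological findings will be extracted from the radiology reports (PDF) using a set of regular expressions for the selected diseases". Reports that contain the search terms, affirmed or negated, are reviewed by hand. No label for a scan that cannot be assessed is described.

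For validation, the section on the FACTUAL cohort covers decompensation and pneumonia, and the section on VERDICT and CATCH covers decompensation. Statistical Analyses nevertheless says, for each validation cohort, "We will, for all diagnoses, calculate odds ratios, sensitivity, specificity". Background states: "This study introduces an algorithm capable of detecting all 3 conditions in the acute setting".

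**The concern.** Mixing acquisition protocols reduces bias when the label does not depend on the protocol. For embolism it probably does. Suspected embolism is one of the listed indications, and the indication influences how the scan is acquired. A report on a noncontrast scan done for another reason will often say nothing about embolism, and with no category for non-assessable scans that silence becomes a negative label.

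Two features of the plan could turn this into a shortcut. Density measurements can reveal whether contrast was given, and tuning on AUC rewards any feature that separates the labels, including one that recognises scan type rather than emboli.

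The planned checks are poorly placed to catch it. Expert review covers false positives and false negatives, whereas a noncontrast scan called negative is counted as a true negative. No external cohort fills the gap. FACTUAL is noncontrast, excludes patients with "CT thorax already indicated (pulmonary embolism, aortic dissection, or aneurysm", and is not planned for embolism. VERDICT and CATCH lack radiological reports, as the limitations acknowledge.

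At stake is what an internal AUC, or a true negative rate meeting the 90% target, would mean for embolism. It could partly measure recognition of scan type, and the statement that all three conditions can be detected would rest on that figure alone.

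**Working it through.** The article gives no AUC, specificity, prevalence or scan-type share for embolism, and its Power Calculation section contains no formula, so there is no stated figure to reproduce. What follows is illustration under assumptions.

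**Inputs from the article**
- 12,348 scans, 5111 studies, 4672 patients; 12,348 / 5111 = 2.42 scans per study.
- Target: true positive rate and true negative rate of at least 90% (Validation of the AI Algorithm).

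**Assumed inputs**
- w: share of embolism-negative test scans on which embolism cannot be assessed (0.1, 0.3, 0.5).
- Performance within assessable scans, and how easily non-assessable scans are called negative.

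**1. Specificity.** Pooled specificity is an exact mixture:

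pooled = (1 − w) × spec_assessable + w × spec_non-assessable.

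If every non-assessable scan is called negative (spec_non-assessable = 1), a pooled value of 0.90 implies spec_assessable = (0.90 − w) / (1 − w):
- w = 0.1: 0.80 / 0.90 = 0.889
- w = 0.3: 0.60 / 0.70 = 0.857
- w = 0.5: 0.40 / 0.50 = 0.800

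**2. AUC.** The same identity holds: pooled AUC = (1 − w) × AUC_assessable + w × AUC_out, where AUC_out is the probability that a positive scan outranks a non-assessable negative. With AUC_assessable = 0.80:

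| AUC_out | w = 0.1 | w = 0.3 | w = 0.5 |
|---|---|---|---|
| 0.80 (scan types not separated) | 0.80 | 0.80 | 0.80 |
| 0.95 | 0.815 | 0.845 | 0.875 |
| 1.00 (perfect separation) | 0.82 | 0.86 | 0.90 |

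**3. What contrast status alone could achieve.** Let c be the share of contrast scans and p the embolism prevalence among them, and suppose all positives are contrast scans. The rule that calls every contrast scan positive has sensitivity 1, FPR = c(1 − p) / [c(1 − p) + 1 − c] and AUC = (2 − FPR) / 2. With p = 0.10:
- c = 0.9: FPR = 0.81 / 0.91 = 0.890, AUC = 0.555
- c = 0.5: FPR = 0.45 / 0.95 = 0.474, AUC = 0.763
- c = 0.3: FPR = 0.27 / 0.97 = 0.278, AUC = 0.861

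These are AUCs of a rule with no knowledge of emboli. They are not the amount by which a real model's AUC would be raised.

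**4. The opposite direction.** Suppose scan types are not separated, and a share q of the non-assessable negatives are unseen emboli that score like positives. Then AUC = (1 − w) × 0.80 + w × [(1 − q) × 0.80 + q × 0.5]. For w = 0.3 and q = 0.02 this is 0.798; for w = 0.5 and q = 0.10 it is 0.785. The loss is small beside the possible gain in step 2.

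**The case against.** A reader might infer that the embolism model is trained and tested on every extracted scan, that its negative labels are produced by scan type, and that its AUC and specificity are therefore inflated. The documents do not support that much.

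- **Not every scan is used.** Power Calculation says some scans were unusable, among other reasons for incomplete thoracic coverage. The abdominal scans are those that include the lungs, and neither abdominal nor low-dose scans are said to lack contrast. Only the noncontrast part has clear force.
- **Many negatives are genuine.** Scans done for suspected embolism are in the pool. With 2.42 scans per study, a report-level positive may also attach to a noncontrast series, which would break the assumption in step 3 that all positives are contrast scans.
- **The premise is not in the article.** That noncontrast scans do not reliably show embolism is general radiological knowledge, although leaving embolism out of the FACTUAL validation is consistent with it.
- **The size is open.** The results run from no inflation to a substantial amount, depending on unknown inputs.
- **Embolism is secondary.** The article focuses on decompensation, calls the model a foundation for embolism, says embolism labelling is ongoing, and defers technical detail to a separate methods article.
- **There are safeguards.** SHAP plots could expose a dominant density feature, and unclear labels go to clinicians.

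These points limit the certainty and the weight of the finding. They do not remove it. Pooling contrast and noncontrast scans is an affirmative choice, presented as bias mitigation without an exception for embolism, rather than a detail left out. The stated reasons for unusable scans do not mention contrast or assessability. A vascular density feature could look clinically plausible in a SHAP plot and survive.

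**Conclusion.** The concern holds as a risk. As written, the plan lets noncontrast scans count as embolism-negative by default and gives the model features that can recognise them. Pooled AUC and true negative rate may therefore overstate performance in scans where embolism can be assessed. Inflation is the likelier direction but is not certain.

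The size cannot be fixed from the article. Under the stated assumptions, a model that just meets the 90% true negative target overall could have a specificity of 0.89 to 0.80 in assessable scans, for non-assessable shares of 10% to 50%. If the model does not separate scan types, there is no inflation.

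Separately, the promise in Statistical Analyses to report metrics for all diagnoses in each validation cohort does not fit the cohort sections, which plan no external validation of embolism. The point should be addressed, but it does not touch the primary focus on decompensation or the completed congestion model.

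**What to change.** 1. In Training and Internal Validation Cohort and Development of the AI Algorithm, restrict embolism training, thresholding and internal testing to contrast-enhanced scans in which the pulmonary arteries are assessable. At minimum, report embolism AUC, sensitivity and specificity within those scans as the main result, with the pooled figures secondary.
2. In Statistical Analyses, name the diagnoses evaluated in each cohort, in line with the cohort sections: decompensation and pneumonia in FACTUAL, decompensation in VERDICT and CATCH.
3. In Background, limit the claim for embolism to internal validation. The Conclusions section does not name embolism and needs no change on this point.

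The cost is modest while embolism labelling is unfinished: fewer scans for that model and probably a less favourable headline figure. Contrast status would have to be read from image headers or the acquisition protocol, because Ethical Considerations lists indications, radiographic diagnoses, sex and age among the information collected, but not contrast or acquisition phase.
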